## Methods/Design

### Objectives

*Masihambisane *is a cluster RCT to test the effectiveness of Peer Mentor support in addressing health, mental health, and stigma challenges faced by WLH. The challenges of chronic illnesses, mental health symptoms, infant feeding and treatment are confronted by WLH on a consistent, daily basis, therefore no single outcome can definitively validate the effectiveness of this Peer Mentor program. We focus on cumulative change across 15 indicators of maternal and infant health. The health-protective behaviors of WLH are documented over time and compared to the baseline rates. These indicators range in their uptake, for example, 92% of babies receive their vaccinations on time, however, infant HIV testing and receipt of results occurs less frequently.

We hypothesize that WLH and their infants in the intervention clinics, compared to WLH who receive standard PMTCT care, will have:

- higher maternal knowledge about HIV self-management;

- better maternal ARV adherence antenatally and at the time of birth;

- increased HIV testing of their baby at six weeks and receipt of test results;

- adherence to regular health visits and TB testing;

- infant weight of more than 2500 grams at birth with normal growth and development for 12 months;

- greater mental health, social support, and ability to cope with HIV stigma;

- higher rates of HIV testing among sexual partners; and

- higher rates of condom use with partners of serodiscordant HIV status.

In order to achieve statistical significance in the analyses, we need to recruit 1200 pregnant WLH (150 per clinic at 8 clinics) with 600 in the intervention and 600 in the standard-of-care control clinics. Enrollment criteria are: 18 years or older at the time of first assessment, less than 34 weeks pregnant at intake, HIV seropositive, and enrolled in the PMTCT programme at one of the eight study clinics. In addition, prospective participants are asked to indicate their intention to reside in the area for the duration of the study, and they must be able to give informed consent, as judged by the interviewer.

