### Data Analysis

WLH are assessed at six days, six months, and twelve months post-birth. Outcomes are compared to health care data routinely collected for mother and child.

The primary outcome is a composite score calculated as the sum of indices for the presence (1) or absence (0) of maternal and child health and well-being. Indices encompass five domains. 1) **
*Child health status *
**includes birth weight and length being within one standard deviation of World Health Organization (WHO) standards, normal development according to WHO norms for motor milestones, absence of FAS symptoms, and positive parenting as assessed by the Parenting Stress Index short form [39] and a bonding questionnaire [40]. 2) **
*Healthcare and health monitoring *
**include the number of antenatal, postnatal, and HIV-related clinic visits. Monitoring includes understanding CD4 count and adherence to all prescribed anti-retrovirals. 3) **
*HIV transmission-related behaviors *
**include disclosure of HIV test results to partners, requesting partners to test, consistent use of condoms, use of single feeding method until six months, baby testing at six weeks, baby prescribed and administered antibiotics at six weeks, maternal AZT during pregnancy, infant NVP at birth and AZT after birth, and disclosure of baby's status to partner or family. 4) **
*Mental health *

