**includes the Edinburgh Postnatal Depression Scale [40] and the General Health Questionnaire. 5) **
*Social support *
**includes an adapted scale from Barrera [41] assessing instrumental, emotional, and childrearing support as well as family, neighbour, and community support for healthy acts. The indices are monitored throughout the intervention and at the final assessment.

Intervention effectiveness is assessed by comparing the composite outcome over 12 months between the intervention and standard-of-care control conditions. These composite scores will be compared using multilevel models, i.e., hierarchical models and random effect models, which account for clustering of repeated assessments within individuals and clustering of individuals within clinics [42]. Multilevel models can be applied to normally distributed and non-normally distributed outcomes, we will choose the most appropriate model based on the data. If data transformations sufficiently normalize the composite outcome, e.g., a logarithmic transformation to reduce skewness, we will fit a linear model. If a normal assumption is not appropriate, we will categorize the data and use a longitudinal logistic regression for binary responses [43] and longitudinal ordinal logistic regression to look for shifts in ordinal response levels between the intervention conditions [44]. In all analyses, clustering within clinic will be taken into account, and multiple imputation methods will be used for missing individual outcome scores [45,46].

While the primary outcome composite score will provide a summary of the overall effectiveness of the intervention program, we will also examine each outcome component for a more detailed interpretation. This will be done using longitudinal logistic regression for binary data, to determine whether, and in what direction, the intervention is associated with changes in each component.

Finally, dose-response analysis will be conducted to test for relationships between the number of intervention sessions attended, as well as time of recruitment, and the composite score. The initial patterns of the outcome measures will be examined through descriptive summaries. If necessary, transformations will be conducted to approximate normality, homogeneous variance and linearity in the model.

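### Questionnaire scales and visit counts are analysed component by component only as 0/1 indices; full-scale models on the same data would recover modest power in a secondary analysis

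*Protocol article*

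**What the plan says.** The Data Analysis section of the protocol article defines the primary outcome as "a composite score calculated as the sum of indices for the presence (1) or absence (0) of maternal and child health and well-being". The five domains that feed it mix two kinds of measure:

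- **Binary by nature:** for example disclosure to the partner, baby tested at six weeks, infant NVP at birth, a single feeding method.
- **Not binary by nature:** the Parenting Stress Index short form, a bonding questionnaire, the number of antenatal, postnatal and HIV-related visits, an adapted social support scale, and a mental health domain that "includes the Edinburgh Postnatal Depression Scale [40] and the General Health Questionnaire". Birth weight and length also appear, as an index defined by distance from WHO standards.

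After the composite analysis, the section states that "we will also examine each outcome component for a more detailed interpretation", and then: "This will be done using longitudinal logistic regression for binary data, to determine whether, and in what direction, the intervention is associated with changes in" the separate components. Linear and ordinal models are described for the composite score. No continuous or count model is described for a component, and no cut-off is given for any questionnaire.

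Among the hypotheses in the Objectives section is "greater mental health, social support, and ability to cope with HIV stigma", with no threshold attached.

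**The concern.** A 0/1 form is needed to add unlike items into one score. It is not needed when a component is looked at by itself, and that separate look is where the document seeks its detail. A woman whose depression or support score improves without crossing the cut counts as unchanged, although the hypothesis is about degree.

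The component step is the only analysis named in the article that separates mental health and social support from the composite. With eight clinics, its power is limited to begin with. Cutting the scales lowers it further, so a real shift in scores is more likely to be reported as no effect.

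**Working it through.** **1. The plan's own figure.** The Objectives section says "we need to recruit 1200 pregnant WLH (150 per clinic at 8 clinics"), "with 600 in the intervention and 600 in the standard-of-care control clinics". The arithmetic agrees: 150 × 8 = 1200 and 150 × 4 = 600. No alpha, power, effect size, SD or ICC accompanies the figure, so there is no power statement to reproduce.

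**2. Inputs.**
- From the document: 4 clinics per arm, m = 150 women per clinic, three post-birth assessments.
- Cut at p = 0.30, suggested by the Background section's statement that post-partum depression exceeds 30% in South African townships. This is not a stated cut-off for any scale.
- Assumed: two-sided alpha 0.05, an underlying normal score, shift d = 0.2 or 0.3 SD, ICC ρ = 0.005 to 0.05, within-woman correlation 0.5, no dropout.
- Test: comparison of clinic means by a t test on 8 − 2 = 6 df.

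**3. Variance of a clinic mean, in SD units of the score.**
- Full scale, one visit: V = ρ + (1 − ρ)/m.
- After the cut, one visit (delta method): V = ρ + (R − ρ)/m, with R = p(1 − p)/φ(z_p)² = 0.21/0.3477² = 1.737. The information kept per woman is 1/1.737 = 58%.
- Full scale, mean of three visits: V = ρ + (1 − ρ)(1 + 2 × 0.5)/(3m).
- After the cut, mean of three visits: V = ρ + [(R + 2C)/3 − ρ]/m. Here C is the covariance of two 0/1 values from the same woman, divided by φ(z_p)². It comes from the bivariate normal with correlation ρ + 0.5(1 − ρ); at ρ = 0.01, C = 0.559.

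Power follows from the noncentral t with noncentrality d/√(2V/4).

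**4. One case in full (d = 0.3, ρ = 0.01, one visit).**
- Full scale: V = 0.01 + 0.99/150 = 0.01660; noncentrality 0.3/√0.00830 = 3.29; power 78.3%.
- Cut: V = 0.01 + 1.727/150 = 0.02151; noncentrality 0.3/√0.01076 = 2.89; power 67.6%.
- Loss: 10.7 points.

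**5. All cases, 30% cut (power in %, full scale → cut; losses from unrounded values).**

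| d | ICC | One visit | Loss | Mean of three visits | Loss |
|---|---|---|---|---|---|
| 0.2 | 0.005 | 59.3 → 45.5 | 13.8 | 68.2 → 60.5 | 7.7 |
| 0.2 | 0.01 | 45.4 → 36.9 | 8.6 | 50.7 → 46.1 | 4.6 |
| 0.2 | 0.02 | 31.0 → 27.0 | 4.0 | 33.3 → 31.3 | 2.0 |
| 0.2 | 0.05 | 17.2 → 16.2 | 1.0 | 17.7 → 17.3 | 0.4 |
| 0.3 | 0.005 | 90.3 → 78.4 | 11.9 | 95.0 → 91.1 | 4.0 |
| 0.3 | 0.01 | 78.3 → 67.6 | 10.7 | 83.6 → 79.0 | 4.5 |
| 0.3 | 0.02 | 58.7 → 51.9 | 6.9 | 62.3 → 59.2 | 3.1 |
| 0.3 | 0.05 | 32.6 → 30.4 | 2.2 | 33.6 → 32.7 | 0.9 |

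**6. Sensitivity to method.** A simulation at d = 0.3 (3000 runs) gave losses of 14, 13, 10 and 2 points for one visit and 5, 5, 4 and 2 for three visits, in the same ICC order. A normal approximation at d = 0.2, which ignores the small number of clinics, gave 17, 12, 7 and 2 points for one visit. A 6-df calculation at d = 0.3 that moves the proportion with the shift gave 14.5, 13.5, 9.4 and 3.9. The table can thus be off by a few points; the direction and the decline from ICC 0.01 upwards are the same throughout.

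These figures describe roughly normal scale totals. No loss was computed for visit counts, where the argument is qualitative.

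**The case against.** **The loss is small for the outcomes that matter here.** The scales are to be modelled longitudinally, so the three-visit column is the closer guide, and it shows 2 to 8 points at ICC up to 0.02 and under 1 point at 0.05. This stands, and it sets the weight of the point. A reader might infer a loss of 20 points or more for the scales. Such figures arise with a 17% cut or zero clustering. The document links 17% to birth weight below 2500 g, not to any questionnaire.

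**Birth weight.** A reader might extend the criticism to birth weight. The document does not support this. The Objectives section states that hypothesis as a threshold (above 2500 g), so a binary test matches it. The index listed under Data Analysis is a different cut, within one SD of WHO standards, so a power loss modelled on a 17% cut does not describe the planned index either.

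**Coherence with the composite.** Analysing the indices in the form in which they enter the sum shows which items drive it. That is a fair reason to keep the binary analyses, but not a reason to have nothing else for the scales.

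**A fuller plan may add models.** The article excludes no further analysis, so a reader should not infer that full-scale analyses are ruled out. A later sentence does allow transformation of outcome measures towards normality, but it sits in the dose-response paragraph, which concerns the composite. What the article does state is one method for every component. The point rests on that stated choice, not on a gap.

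**Conclusion.** The point holds for the five questionnaire measures and the visit counts. The named method reduces them to 0/1 in a step where nothing requires it, and the mental health and support hypothesis sets no threshold.

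Under the assumptions above, the cost is about 4 to 14 points of power for a single assessment and about 2 to 8 points for three averaged visits, at ICC 0.005 to 0.02. At ICC 0.05 it is about 2 points or less. Effect size, ICC, within-woman correlation and cut are all assumed, so these ranges illustrate the cost and are not properties of the trial. That information is lost does not depend on them.

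It would be wrong to conclude that the primary result is compromised. The component analyses are secondary and interpretive, the composite needs its 0/1 coding, and components that are binary by nature lose nothing. This is a cheap improvement, not a defect that threatens the trial.

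**What to change.** In the paragraph of Data Analysis that deals with the components:

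- Keep the 0/1 indices for the composite, and logistic regression for components that are binary by nature.
- Analyse the depression, general health, parenting stress, bonding and social support totals on their full scale, with the multilevel linear model already named (random effects for clinic and woman).
- Analyse the numbers of clinic visits with a count model that also allows for clinic.
- Report the proportion past each cut as a supplement, so that the link to the composite remains visible.
- Keep a binary test for the 2500 g birth-weight hypothesis; continuous birth weight is at most an addition.

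The cost is a change of wording and a few extra model fits, with no new data. Mean differences on a scale are less immediately interpretable than proportions, which the supplementary proportions cover. If the clinic ICC is near 0.05, the gain in power will be slight.

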#### *Masihambisane *Intervention

The Peer Mentors work full-time in the intervention clinics and are integrated into the Department of Health PMTCT programme at each site. WLH are invited to attend a series of four antenatal and four postnatal sessions, scheduled to coincide with their routine antenatal and well-baby clinic visits. Sessions last 60 to 90 minutes, and are attended by four to ten WLH who meet to discuss, roleplay, share, and practice strategies to address issues critical to effective PMTCT. Each session proceeds in a similar sequence: WLH arrive, sing and pray together, and share successes and joys from their week. The Peer Mentor shares her triumphs and challenges as a WLH and acknowledges the importance of the support group for her. A topic is introduced for the day's meeting and a brief demonstration of the content message is presented, then the group brainstorms the types of challenges the WLH will encounter if she tries to implement this knowledge in her life. Finally, goals are set for the upcoming week and a song and a prayer end the meeting.

Each of the following issues is covered by the intervention:

1) *Living Positively*. Using a jar with different coloured jelly beans, the Peer Mentor shows that all families in KwaZulu-Natal are affected by HIV and the WLH is not alone, in particular she has support in the group leader and group members. WLH are encouraged to attend all clinic appointments. Women are provided with referral letters to the couple to encourage them to get tested together for STIs. Women discuss to whom they want to disclose their serostatus and roleplay the process of disclosure and asking for emotional support.

2) *Keeping Myself and My Baby Healthy*. The Peer Mentor helps WLH understand why they must avoid smoking and drinking, eat healthily, take vitamins and medicine as prescribed in antenatal care, get regular exercise, seek and maintain social support, and do things they enjoy. A realistic black baby with Fetal Alcohol Syndrome is presented and the characteristics and life-long consequences of alcohol on babies are discussed. A raw egg is broken in a cup of alcohol and women watch as the egg poaches at room temperature to illustrate adverse effects of alcohol on brain development *in utero*.

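### The secondary dose-response analysis uses a plain count of sessions attended, so early delivery, which cuts the count and lowers the birth items, can produce a false positive slope.

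*Protocol article*

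**What the plan says.** The last paragraph of Data Analysis (Methods/Design) states that a "dose-response analysis will be conducted to test for relationships between the number of intervention sessions attended, as well as time of recruitment", with the composite as the outcome. The exposure is a count of sessions, and time of recruitment is named beside it without a definition.

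Four other statements bear on what that count measures:

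- Masihambisane Intervention: "WLH are invited to attend a series of four antenatal and four postnatal sessions, scheduled to coincide with their routine antenatal and well-baby clinic visits".
- Objectives: a woman may enter if she is "less than 34 weeks pregnant at intake".
- Data Analysis: the outcome is a "composite score calculated as the sum of indices for the presence (1) or absence (0) of maternal and child health and well-being". Its items include "birth weight and length being within one standard deviation of World Health Organization (WHO) standards", as well as "maternal AZT during pregnancy, infant NVP at birth and AZT after birth".
- Data Analysis: the healthcare items "include the number of antenatal, postnatal, and HIV-related clinic visits".

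The article does not separate antenatal from postnatal sessions in this analysis. It does not set attendance against the sessions a woman could have attended before delivery, and it does not restrict the count to sessions held before an item was settled.

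**The concern.** Delivery closes the antenatal part of the programme. For a woman who enters at a given gestation, the date of birth decides how many of the four antenatal sessions she can still reach. The same date drives birth weight and length, which are scored. Short gestation therefore lowers both the dose and the score, and the regression sees a positive slope that owes nothing to the sessions.

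The count also includes postnatal sessions, which cannot have influenced items already settled at birth, such as birth weight, birth length and infant NVP at birth.

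At stake is the reading of a secondary analysis. The error favours the programme, and a positive dose-response is easily taken as support for a causal effect of attendance.

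**Working it through.** **The plan's own figures.** The article gives no number for this analysis. The sample size is internally consistent (8 × 150 = 1200; 4 × 150 = 600 in the intervention arm), so 600 women are the natural set for a dose-response model.

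**Inputs from the article.** Up to four antenatal and four postnatal sessions; entry below 34 weeks; 15 indicators scored 0/1 (Objectives); 17% of babies below 2500 g (Background), used to calibrate.

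**Assumptions not in the article.** Entry uniform over a stated range. 15% of births uniform over 31 to 37 weeks, the rest normal with mean 39.5 and SD 1.2 weeks. Birth weight = 3080 + 150 × (gestation − 39.5) g, residual SD 420 g. Length = 49.5 + 0.8 × (gestation − 39.5) cm, residual SD 1.8 cm. Postnatal sessions Binomial(4, 0.6). The other 13 items independent at 60%. No clinic effect and **no effect of sessions**. About 19% of simulated babies fell below 2500 g.

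**Step 1: composite regressed on total sessions.** Birth items were scored as at least 2500 g and at least 47 cm, with no visit-count item. Each line rests on 1000 runs of 600 women. Cells give the false slope per session and the rejection rate at two-sided 5%.

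| Entry (weeks), visit interval, attendance | Count only | + gestation at entry | + gestation at entry and at birth |
|---|---|---|---|
| 14–34, 4 weeks, 70% | 0.068, 31% | 0.106, 41% | 0.000, 6% |
| 24–34, 4 weeks, 70% | 0.104, 43% | 0.120, 49% | 0.001, 4% |
| 24–34, 4 weeks, 100% | 0.148, 74% | 0.204, 87% | 0.006, 6% |
| 28–34, 3 weeks, 80% | 0.148, 74% | 0.167, 80% | 0.000, 5% |

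If only birth weight depended on gestation, the count-only slope was 0.03 to 0.07 and rejection 7 to 24%.

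**Step 2: birth items as worded, two-sided within one SD.** Two further null simulations, each with a total count of 0 to 8 and 15 items, gave 0.04 to 0.12 points per session with 13 to 64% false positives, and 0.04 to 0.16 points with 20 to 79% at 70% attendance. Together these give the range quoted in the verdict.

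**Step 3: why a small slope rejects so often.** The composite SD is about 1.9, so 0.04/1.9 ≈ 0.02 SD and 0.16/1.9 ≈ 0.08 SD per session. The postnatal count has variance 4 × 0.6 × 0.4 = 0.96. With an antenatal variance of about 1 (assumed), the SD of the total is about √1.96 = 1.4. The standard error of the slope is then 1.9/(1.4 × √600) ≈ 0.055. A false slope of 0.104 is 0.104/0.055 ≈ 1.9 standard errors, which rejects nearly half the time. The second line of the table gives 43%.

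**Step 4: checks on the mechanism.**

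- With the link between gestation and birth weight removed, rejection returned to about 5 to 6% for the count alone.
- The postnatal count alone had a slope of about zero on the birth-weight item.
- With entry at 12 to 24 weeks, two-weekly visits and 80% attendance, the mean antenatal count was 3.97 and the bias nearly vanished: rejection was 8% on the birth-weight item and 6% on the composite.

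**Step 5: visit counts.** Sessions are held at the visits that the composite also counts. With an antenatal visit item scored, the count-only slope was 0.21 to 0.33 (96 to 100% rejection). After adjustment for gestation at entry it was 0.20 to 0.29 (91 to 99%). Adding gestation at birth still left 8 to 55%.

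**The case against.** **Article-level detail.** This is one sentence in a condensed article, and splitting or lagging the count is normally left to the analysis plan. A cumulative count at each assessment would fit the repeated-measures models. That is fair as far as it goes. But the article does fix the exposure as a number of sessions and the outcome as the composite, and a cumulative count would still be cut short by delivery.

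**Size.** A reader might infer a large distortion from birth weight alone. A null calculation of birth weight above 2500 g on antenatal sessions only gives false odds ratios of 1.29 to 2.23 per session. That is not the planned analysis: the plan uses all sessions and the composite, and its scored weight item is a one-SD band. On the composite the slope is modest. This objection stands, and the verdict uses composite figures only.

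**Adjustment makes it worse.** A reader might also infer that including time of recruitment enlarges the bias. That holds only if the term means gestation at entry, which the article does not say, and only if no visit count is scored. What does stand is that the term fixes at most the start of the antenatal window, never its end.

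**Postnatal sessions.** They do not create the gestation bias. They only add exposure that cannot be causal for birth items.

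**Consequences.** The article speaks of testing for relationships. It does not claim that sessions cause better outcomes, and it does not say the result will set the number of sessions in a roll-out.

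**Conclusion.** The point holds for the secondary dose-response analysis. As worded, that analysis can show a positive slope when sessions have no effect, because delivery ends antenatal attendance and also determines birth weight and length.

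Under the assumed gestation and attendance patterns, the false slope on a 15-item composite is about 0.04 to 0.16 points per session, and the false-positive rate about 13 to 79% against a nominal 5%. The size depends on gestation at entry, visit interval, attendance and how many birth items are scored, and the article gives no distribution for the first three. The bias is near nil if almost all women finish four antenatal sessions well before birth. The article gives reason to doubt that: entry is open to just under 34 weeks, and the Background reports that only 54% of women begin antenatal care before the third trimester.

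A reader might infer that the trial's conclusion on effectiveness is compromised. The documents do not support that: it rests on the comparison of randomised arms, which does not use attendance.

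**What to change.** In the dose-response paragraph of Data Analysis:

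1. Relate each composite item only to sessions attended before that item was determined: antenatal sessions for birth and delivery items, sessions before six weeks for six-week items, and so on.
2. Condition on the number of sessions open to the woman between enrolment and that point. Alternatively, use a landmark: sessions attended in a fixed interval after enrolment, among women still pregnant at its end.
3. Leave birth weight, birth length and the clinic-visit counts out of any model that uses the total count.
4. Report the result as a non-randomised association.

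In a null simulation of the composite, conditioning on sessions available before birth brought false positives back to about 3 to 7%. For the birth-weight item on antenatal sessions alone, it gave odds ratios of 0.92 to 1.09 with two- or four-weekly sessions but left 1.03 to 1.34 with weekly ones. The landmark is the safer choice if sessions turn out to be that frequent.

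The cost is wording only. Attendance is recorded at every session, the delivery date is extracted from the records, and the baseline interview can date enrolment. The downside is a less precise and probably weaker dose-response estimate. Conditioning on available sessions would also hide part of any real effect that worked by prolonging gestation.

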Three tools are used in all intervention sessions. To increase awareness and skills for emotional regulation, WLH are taught to use *Feeling Cups *to calibrate their feelings. A clear glass is filled with different levels of water, depending on their degree of uncomfortable (full) feelings. *Tokens *are exchanged between members. These are small chips that indicate positive feelings towards one or more group members. Finally, WLH are provided with an *empty jar and beans *to count the number of times they adhere to their goals.

We have developed a variety of materials, manuals, and videos on PMTCT. Workbooks for pregnant women were adapted for HIV, alcohol and malnutrition content from existing evidence-based interventions [8]. All materials are in Zulu, after being translated and back-translated into English to ensure their accuracy and appropriateness. The colours and images were selected by the intervention team, the Peer Mentors, and the Community Advisory Board. In designing these learning aids, we followed the process for developing materials in Tanzania [38] where "job aids" were developed that are culturally tailored, easy to use, and feasible to distribute. All materials were used in the pilot interventions and we debriefed pregnant WLH, nurses in health clinics, and supervising Peer Mentors in development of the materials to ensure cultural appropriateness.

No incentive is given for participating in the intervention sessions, but participants receive tea and biscuits on arrival, and R30 (about $3.50) towards their transportation costs. Several sessions are held per day at the clinic and are rotated, to enable women to attend any session on the same day as their routine health care appointments. Attendance data is collected at all sessions.

Quality control is managed at three levels: 1) within the clinic by the site coordinator; 2) across clinics by the centralized Intervention Coordinator; and 3) monthly and quarterly by international and domestic intervention specialists. A checklist is completed by the Intervention Coordinator when observing Peer Mentors' groups and provided during routine supervision to Peer Mentors.

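### The dose-response analysis relates sessions attended to a composite that counts the same clinic trips, so a positive slope is expected even if sessions do nothing

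*Protocol article*

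**What the plan says.** Four statements in the protocol article bear on this point.

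- **Exposure and outcome.** The last paragraph of Data Analysis states that "dose-response analysis will be conducted to test for relationships between the number of intervention sessions attended". The exposure is thus sessions attended (0 to 8). The outcome, named later in that sentence, is the primary composite, and recruitment timing is listed there as a further factor whose relationship with the composite is tested.
- **Composite.** Data Analysis defines it as a sum of 0/1 indices over five domains. The healthcare domain covers "the number of antenatal, postnatal, and HIV-related clinic visits". The transmission domain adds items that need a visit, among them "baby testing at six weeks, baby prescribed and administered antibiotics at six weeks".
- **Timing of sessions.** Under Masihambisane Intervention, the four antenatal and four postnatal sessions are "scheduled to coincide with their routine antenatal and well-baby clinic visits". The same section says that sessions are rotated so that any of them can be attended on an appointment day.
- **Safeguards.** Data Analysis states that clinic clustering is accounted for in all analyses and that missing scores are multiply imputed. It does not exclude visit items from the dose-response analysis.

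**The concern.** Three features make the slope hard to read as an effect of sessions.

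1. **Shared trips.** A woman who comes for a routine visit can attend a session that day, and the visit also counts towards the composite. Part of the outcome is generated by the same event as the exposure.
2. **Self-selection.** Women who seek care more readily attend more sessions and are likely to do better on other items, such as adherence and infant testing.
3. **Order in time.** Postnatal sessions come after birth weight, maternal AZT in pregnancy and infant NVP at birth, all of which are in the composite. They cannot have caused those items, yet they count in the dose.

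All three can produce an association without any benefit, and the first two push it upwards. The risk is that a positive slope would be read as corroborating the Peer Mentor programme when it would probably have appeared anyway.

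**Working it through.** **No figure to reproduce.** The article gives no effect size, SD or expected slope for this analysis. The check is whether a slope appears when sessions have no effect on anything.

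**Inputs from the article.** 600 intervention women; 4 antenatal and 4 postnatal sessions on visit days; 15 indicators (Objectives), summed as 0/1.

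**Assumptions, not in the article.** Only intervention women are analysed. There are 4 antenatal and 4 postnatal visits, each made with probability 0.65, and a session is attended on 0.70 of visit days. A visit item scores 1 if at least 3 of the 4 visits of its type are made. All other items are independent of attendance. Clinic clustering is ignored.

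**Hand calculation, one visit item of 15.** Let N be antenatal visits, Binomial(4, 0.65), let V = 1 if N ≥ 3, and let S be sessions attended.

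- P(N=3) = 0.3845 and P(N=4) = 0.1785, so P(V=1) = 0.563.
- Cov(N,V) = (3 × 0.3845 + 4 × 0.1785) − 2.6 × 0.563 = 1.867 − 1.464 = 0.404.
- Cov(S,V) = 0.70 × 0.404 = 0.283.
- S is Binomial(8, 0.455), so Var(S) = 8 × 0.455 × 0.545 = 1.984 and the SD is 1.408.
- Spurious slope = 0.283 / 1.984 = 0.142 composite points per session.
- With 14 other independent items at 50% prevalence, the composite SD is √(0.563 × 0.437 + 14 × 0.25) = 1.935.
- r = 0.142 × 1.408 / 1.935 = 0.104; z = 0.104 × √598 / √(1 − 0.104²) ≈ 2.55. The chance of p < 0.05 is about 72%, or about 79% if the other items have 70% prevalence.

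A simulation in which all women had the same visit propensity gave slope 0.140, r = 0.104 and 72% significant. There is no confounding in that setting, so the shared trip alone produces the slope. With two visit items (antenatal and postnatal) the slope doubles to 0.285, and the simulated rejection rate was 100%.

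**Wider null simulations** (600 women; 300 or 400 runs per setting)

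| Setting | Significant at 5% | r |
|---|---|---|
| 1 visit item of 15, varied cut-offs and session uptake | 57% to 99% | 0.09 to 0.17 |
| 2 or 3 visit items of 15, same variations | 99% to 100% | 0.18 to 0.41 |
| 1 visit item of 20; of 25 | 78%; 67% | 0.11; 0.10 |
| Separate set of runs: 1 of 15 | 64% | 0.09 |
| Separate set: separate visit types, 24 items | 77% | 0.11 |
| Separate set: 1 of 24 | 29% | 0.06 |

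The 29% is not a floor. If 24 items at 70% prevalence had mutual correlation 0.1, the composite SD would be √(24 × 0.7 × 0.3 × (1 + 23 × 0.1)) = 4.08. The hand calculation then gives r = 0.142 × 1.408 / 4.08 = 0.049 and about 23%.

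**Removing the visit items.** With 15 indices and the other items independent of attendance, rejection returned to 3.3% to 8.0% with r about 0. When the other items shared a modest care-seeking tendency (log-odds 0.2 per SD), rejection stayed at 98% to 100% with r of 0.16 to 0.24. Overlap and confounding are therefore separate problems, and dropping the visit items cures only the first.

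**The case against.** The strongest reply has four parts.

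- **The analysis is supplementary.** Effectiveness is judged by the randomised comparison of the composite, and the dose-response analysis gets one closing sentence with no confirmatory claim attached. Covariates can be left to a fuller plan. This stands and limits the importance of the point. But the article itself fixes both exposure and outcome, and a plan that followed it would inherit the overlap.
- **Time of recruitment is named.** It speaks to late entrants having fewer antenatal sessions open to them. It is listed as another factor to test, however, and even as a covariate it would not remove shared trips or care-seeking.
- **The size is uncertain.** This stands. The article states 15 indicators but gives no cut-offs and no number of visit items. Sessions are tied to antenatal and well-baby visits, not to HIV-related ones, so the overlap is partial. A reader might infer that a strong, near-certain false slope has been shown; the documents do not support that.
- **Visits are a legitimate outcome.** Objectives lists better adherence to health visits among the hypotheses, and Data Analysis examines each component separately. This stands for the randomised comparison.

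A reader might also infer that the main comparison is compromised because session "participants receive tea and biscuits on arrival, and R30 (about $3.50) towards their transportation costs". The documents do not support that. The payment is openly described as part of session delivery, the trial randomises the whole package, the article does not say whether control women receive other payments, and it gives no figure for the effect of the money on visits.

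**Conclusion.** The point holds for the dose-response analysis alone. As written, exposure and outcome share clinic trips and attendance is self-selected, so a positive slope is expected under no benefit and cannot by itself support effectiveness.

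The direction follows from the text. The size rests on assumed attendance, cut-offs, item counts and item correlations: about 29% to 99% false-positive results in the simulations with one visit item, and about 77% to 100% with two or three. The spurious slope was about 0.11 to 0.45 points per session in the 15-item settings without confounding. The simulations treat women as independent and the composite as a single score per woman, so they do not reproduce the planned multilevel model.

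The randomised primary comparison is not affected and need not drop the visit items.

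**What to change.** For the dose-response analysis only:

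1. Exclude the visit-count items from the composite. As a sensitivity analysis, also exclude items that need a clinic visit, such as infant testing and antibiotics at six weeks.
2. Relate antenatal items and items fixed at birth only to the number of antenatal sessions attended.
3. Adjust for time of recruitment and for baseline characteristics already collected in the first interview.
4. Report the result as a descriptive association, not as evidence of effectiveness.

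The cost is one extra version of the outcome, a few lines of wording and a weaker claim. Residual confounding by care-seeking remains, which is why step 4 is needed even after steps 1 to 3.

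Replacing the analysis with an instrumental-variable estimate, using randomised arm as the instrument, is not recommended. With arm as the only instrument it essentially rescales the arm difference by mean attendance and cannot test dose-response. It also assumes that arm acts only through sessions, whereas the Recruitment section has women in intervention clinics meeting a Peer Mentor before enrolment and outside the sessions.
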